### Data monitoring

A data safety monitoring board (DSMB) has been convened. This comprises an international expert in impetigo, a local expert in paediatric infectious diseases, and a statistician. An interim safety analysis blinded to allocation will be performed after recruitment of 150 participants. If concerns are expressed, the unblinded data may be made available to the DSMB on request. Stopping criteria may include slow accrual, poor data quality, unacceptable adverse events, and emerging information that makes the trial irrelevant. The DSMB will discuss the outcome of the analysis with the trial steering committee. The unblinded data, apart from the outcome of the DSMB decision, will not be made available to the authors prior to the completion of the trial and unblinding.

### Harms

Any adverse event will be reported; these are defined as any untoward medical occurrence in a subject without regard to the possibility of a causal relationship after entry into the study and until the completion of the study. At day 2 and day 7 of the trial, a safety check is performed by the school nurse to assess for rapid worsening of the impetigo or for adverse effects. If these occur, then the participant can be withdrawn from the trial at the discretion of the nurse. On day 2 and day 7, participants and/or caregivers are directly questioned regarding specific harms including itch, pain, redness, or any other adverse effects of medication. Any requirement for additional medical intervention is considered a potential harm. All harms will be reported.

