### Modifications

All adverse effects, including pain, itch, or allergy to study medication, will be reported; the study medication must be withdrawn and the patient changed to routine treatment as per the SOP of the health clinic. If clinical deterioration while on study medication is identified by the school nurse, the study medication may be withdrawn at the nurse’s discretion. In this case, the patient will be changed to routine treatment as per the standard operating procedures of the health clinic.

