### Primary outcome methods

The primary outcome of this trial is treatment success based on comparison of digital photographs taken at days 0 and 7. If clinical assessment leads to early discontinuation of the trial medication, this is also considered unsuccessful treatment. To aid standardisation, the primary outcome uses digital photographs independently assessed by blinded reviewers. The single largest lesion is photographed prior to commencing treatment, using a digital camera at a distance of 15 cm with an adhesive paper tape measure and unique study ID placed next to the lesion. Three digital images are taken at each data collection visit, and all are submitted to the study investigators. The single best quality image is then selected by the lead investigator (SP) for outcome assessment. Pairs of images are presented to three individual assessors blinded to intervention arm. The method of image presentation is randomised such that assessors are unaware of which image was taken first and which second. The outcome will be treatment success if the images are considered healed or improved and treatment failure if they are the same or worse, or if the reviewers cannot determine the outcome based on the digital images (e.g. due to poor quality images). Where there is discordance between assessor opinions, the majority opinion of two out of three reviewers will be considered the correct assessment. Patients removed from the trial protocol by school nurses or general practitioners before 7 days due to clinical deterioration will also be considered treatment failures. This process has been standardised previously in another large RCT of treatment of impetigo in remote access locations; different from our multicentre urban setting [21].

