### Clinical assessments

Clinical assessments are standardised and recorded on the existing skin assessment database used for school health clinics. A written description of the location of the lesions and identification of the primary lesion being used for assessment is recorded. A paper template is also provided to allow nurses the option to mark on a diagram the location of the lesions.

Seven days after commencing the trial (day 7), the participant is re-assessed by the school nurse, who also records whether the lesion has improved. Both child and caregiver are asked to comment on their satisfaction with treatment and any adverse events related to the medication, including itch, pain, or allergy. School records are checked for absence over the prior 7 days.

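### Two sections disagree on whether a worsening child or one with an adverse effect leaves the treatment or the trial, so day-7 secondary and harm data can be lost in children doing badly

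*Protocol article*

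**What the plan says.** All references are to the protocol article.

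- **Harms.** The school nurse checks for rapid worsening or adverse effects on days 2 and 7. "If these occur, then the participant can be withdrawn from the trial at the discretion of the nurse". Adverse events count "after entry into the study and until the completion of the study", and the questioning is scheduled: "On day 2 and day 7, participants and/or caregivers are directly questioned regarding specific harms including itch, pain, redness".
- **Modifications.** After an adverse effect, "the study medication must be withdrawn and the patient changed to routine treatment as per the SOP of the health clinic". After deterioration, "the study medication may be withdrawn at the nurse’s discretion". Neither sentence takes the child out of the trial.
- **Primary outcome methods.** Two rules deal with early stopping. The first: "If clinical assessment leads to early discontinuation of the trial medication, this is also considered unsuccessful treatment". The second says that children taken off the trial protocol "before 7 days due to clinical deterioration will also be considered treatment failures".
- **Secondary outcomes.** Nurse opinion, participant or caregiver opinion, bacterial eradication and new resistance are all day-7 measures. School absence and adverse events are also compared between arms.
- **Clinical assessments.** Absence does not depend on the child's attendance at the visit: "School records are checked for absence over the prior 7 days".
- **Allocation concealment mechanisms and implementation; Discussion.** Nurses and participants know the arm, and the Discussion concedes a potential bias from early removal for treatment failure.

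**The concern.** Stopping a treatment and leaving a trial have different consequences for the data. A child who stops treatment can still be seen, questioned and swabbed on day 7. A child withdrawn from the trial may not be, and nothing in the article says that such a child is still assessed. Two nurses with the same case could therefore act differently, each following the text.

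The children at risk of being lost are those with worsening lesions or adverse effects. If they drop out of the day-7 comparisons, nurse-rated and caregiver-rated improvement and eradication are estimated in a group from which poor responders have been removed, and later harms in the same children go unrecorded. If removal is more frequent in a less effective arm, that arm looks closer to fusidic acid than it is. In a trial built to show non-inferiority, that is the unsafe direction for results read alongside the primary outcome.

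**Working it through.** **1. The rules side by side**

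| Event | Modifications | Harms |
|---|---|---|
| Adverse effect | Study medication withdrawn, mandatory | Participant withdrawn from the trial, discretionary |
| Worsening | Study medication withdrawn, discretionary | Participant withdrawn from the trial, discretionary |

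The sections differ on what is withdrawn in both rows, and on whether the nurse has a choice in the first row. The Harms wording does not look like a slip: Primary outcome methods speaks of patients removed from the trial protocol, and the Discussion of children removed from the study early.

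**2. What can be lost after trial withdrawal at the first check**

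- Can be lost: day-7 harm questioning, nurse opinion, participant or caregiver opinion, and the day-7 swab (eradication and resistance).
- Not lost: the event that triggered withdrawal, which is seen at that check, and school absence, which comes from records.
- Primary outcome: removal for deterioration, and medication stopped on clinical assessment, count as failure. Whether clinical assessment covers a child stopped for itch or allergy alone is not clear.

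**3. Share of the harm window lost**

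Participant timeline allows the day-2 check to fall on days 2 to 4. The share of the 7 days lost is (7 − d)/7:

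- d = 2: 5/7 = 71%
- d = 4: 3/7 = 43%

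**4. Illustration for nurse-rated improvement**

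The article gives no withdrawal rate by arm. Its only related figure is the overall 10% allowance for loss and exclusions in Sample size (160/0.90 = 177.8, hence 178 per group), which is not split by arm or cause.

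Assumptions: true day-7 improvement is 80% on fusidic acid (the efficacy assumed in Sample size, borrowed here for a secondary outcome) and 70% on a comparator. A fraction e of each arm is removed early, all of them non-improvers, and they are left out of the analysis. Observed improvement is then s/(1 − e), where s is the true proportion.

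| Removed, fusidic acid / comparator | Observed, fusidic acid | Observed, comparator | Apparent deficit (true: 10.0) |
|---|---|---|---|
| 5% / 5% | 0.80/0.95 = 84.2% | 0.70/0.95 = 73.7% | 10.5 points |
| 10% / 10% | 0.80/0.90 = 88.9% | 0.70/0.90 = 77.8% | 11.1 points |
| 5% / 10% | 0.80/0.95 = 84.2% | 0.70/0.90 = 77.8% | 6.4 points |
| 2% / 10% | 0.80/0.98 = 81.6% | 0.70/0.90 = 77.8% | 3.9 points |
| 10% / 5% | 0.80/0.90 = 88.9% | 0.70/0.95 = 73.7% | 15.2 points |

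Equal removal changes the difference little. Unequal removal can shrink or widen it, depending on which arm loses more children.

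**The case against.** The strongest reply is that the article never says follow-up ends at the event. Withdrawal is discretionary, harms are defined up to the end of the study, and all harms are to be reported. Modifications can be read as the operative rule, with Harms worded loosely. Follow-up after stopping treatment, and missing-data rules for secondary outcomes, are details that an article often leaves to the full protocol or the analysis plan.

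Much of this stands. It limits the point to what can happen under the text. It does not remove the contradiction, which is in the printed wording and which an unseen document cannot resolve. The absence of a missing-data rule for secondary outcomes is not itself the finding.

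Three stronger readings are tempting, and the documents do not support them:

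- *All day-7 secondary outcomes are lost.* School absence comes from records, and the triggering harm is already observed.
- *The loss is unequal by arm.* Unblinded nurses and the bias conceded in the Discussion make this plausible, but no rates are given. Adverse-effect removals might fall more on the medicated arms, including fusidic acid, and deterioration on the least effective arm, so the net direction is unknown.
- *The wound-care arm escapes the adverse-effect trigger because it has no study medication.* In Modifications, the reference to study medication attaches most naturally to allergy. Pain and itch can occur in any arm, and the trigger in Harms is neutral between arms.

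A reader might also infer that the primary result is compromised. The two failure rules largely prevent that. In addition, Statistical analyses excludes only children without primary outcome data or whose caregivers withdrew consent, not children withdrawn by the nurse as such.

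**Conclusion.** The point holds in this limited form. Harms and Modifications contradict each other on whether the treatment or the trial is stopped and, for adverse effects, on whether stopping is discretionary. Following Harms can cost the day-7 harm questions, nurse and caregiver opinion and the swab in children doing badly, and 43% to 71% of the harm window for a child removed at the first check. The loss may differ by arm.

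The effect on the secondary comparisons cannot be estimated from the article. Under the stated assumptions (80% against 70%, only failures removed and then omitted), a 10-point deficit would appear as 6.4 points with 5% against 10% removal and as 10.5 points with 5% in both arms. No non-inferiority margin is set for nurse or caregiver opinion, so these figures show distortion of an estimate, not a wrong non-inferiority conclusion. The wording should be amended; the primary outcome is only marginally affected.

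**What to change.** 1. Reconcile Modifications, Primary outcome methods and Harms so that stopping study treatment and leaving follow-up are separate events with separate wording. Resolve the mandatory against the discretionary wording for adverse effects at the same time. Which clinical rule should apply, and when treatment stops, is for the trial team; none is proposed here.
2. State that a child who stops study treatment keeps the day-7 assessments already scheduled (harm questions, nurse and caregiver opinion, photograph and swab) unless the caregiver withdraws consent.
3. Count removal for deterioration as failure for nurse- and caregiver-rated improvement, as Primary outcome methods already does for the primary outcome. State there whether stopping for an adverse effect alone falls under its clinical-assessment rule.

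The cost is amended wording, one analysis sentence and a few extra attendances at a visit that already exists. The downside is that these children will be on routine care by day 7, so their swab results should be labelled as reflecting that care.

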### Auditing

Regular visual review of the data will be performed by the lead investigator (SP) for completeness and quality of the data.

## Discussion

The aim of this study is to investigate the relative effectiveness of non-antibiotic management of impetigo in children. The use of existing school health clinics located within the more socioeconomically deprived communities in Auckland, NZ, allows access to a large population of children within a community who might not otherwise seek medical help. This ensures access to an appropriate cohort of children at high risk of impetigo.

Engaging authentically with Māori and Pacific communities is vital  to the success of this project. As outlined above, Māori and Pacific communities living in New Zealand face barriers to accessing appropriate and timely primary healthcare for potentially preventable conditions such as impetigo [14]. Research is critical to address these inequities and should be undertaken in a culturally appropriate way using a partnership approach with Māori and Pacific researchers. School nurses who are known and trusted by the families, and representative of the school communities, will be important to ensure effective engagement.

The National Hauora Coalition (NHC), a Māori primary health organisation, was consulted early in study design. A Māori nurse leader (AG) directed key trial implementation and engendered the support of the school nurses who represent both Māori and Pacific Island healthcare workers. Information leaflets have been provided in multiple languages, including Te Reo Māori, Tongan, and Samoan, and nursing staff provide additional verbal information as a more acceptable communication [14]. Specific acts of recognition and practical reimbursements have been shown to contribute significantly to a sense of value and reduce the financial strain when accessing healthcare [14]. To acknowledge this, a gift (koha) of a NZ$20 supermarket voucher is offered to each family after completion of the trial.

Because of the large and disparate pool of recruiters, it is important that the primary outcome is as comparable and unbiased as possible. Digital images allow for centralised assessment despite the distance between recruiting sites. However, this means the existing scoring system (SIRS) is not practical as variables included in the scoring such as warmth, pain, and itch are not amenable to visual assessment alone. For this reason, assessor defined scoring was used. Erythema is also one of the elements of the SIRS scoring system, and when assessing children with darker skin, this is often underestimated [23], leading to minimisation of the severity of lesions in those with darker skin. The use of digital images and multiple reviewers for the primary outcome aims to minimise the bias inherent in the majority of previous studies on impetigo and provide a reproducible outcome, consistent with real world improvement. This remains an imperfect measure as it is dependent on good quality digital images and reviewer defined assessment. Due to the visible difference in the topical medications, neither school nurses nor participants could be blinded to treatment. This introduces a potential element of bias for those removed from the study early due to clinical treatment failure. It was considered unfeasible to introduce a placebo medication to the simple wound hygiene group. Potentially, any ointment without antimicrobial properties could provide an environment for bacterial growth or negatively affect bacterial growth, potentially changing the outcome for this group.

Topical antibiotics remain the mainstay of treatment for mild-to-moderate impetigo in many countries around the world, including New Zealand. Widespread community use and a tendency for prolonged courses mean that they excel at inducing antimicrobial resistance. Evidence for antiseptic use or simple hygiene measures in impetigo is extremely limited: this will be only the second trial to compare these topical antiseptics and antibiotics and the first to take current antimicrobial resistance patterns into account. On the background of a worldwide increase in antimicrobial resistance and with increasing recognition of the importance of antimicrobial stewardship, it is timely to re-address the evidence for the role of antiseptics and antibiotics in the treatment of impetigo. This is only possible, however, if the most affected communities are appropriately engaged in this research.

## Data Availability

Patient consent/assent form is attached. Materials including patient information and data collection sheets are available on request from the authors.
